## Discussion

The first objective of this proposed study will be to analyze the efficacy of the Spanish adaptation of MCP for cancer survivors. For this aim, we have designed an RCT in which we will compare MCP to CBT in people with cancer, with three assessment times: pre-treatment, post-treatment, and 6-month follow-up. In previous studies on the efficacy of MCP, it has been compared to waitlist, TAU, therapeutic massage, and supportive social therapy (8, 9, 12, 13). In order to broaden the knowledge about the efficacy of MCP, in this study we compare it to CBT. In previous studies, CBT has shown its effectiveness in reducing anxiety and depression, facilitating cancer adjustment, and improving quality of life (21, 22). Therefore, if MCP is equally effective or more effective in reducing anxiety and depression and improving quality of life, hopelessness, and meaning in life, this result would suggest that MCP could be a treatment of choice for people with cancer.

The second objective of this proposed study will be to analyze the feasibility and acceptance of MCP in Spanish participants with cancer. The concepts and premises of logotherapy, such as meaning-making, vital goals, the concepts of responsibility, freedom, courage, legacy, and will to meaning, or meaning in life, are subject to cultural, religious, and social factors specific to each culture (19). Given that all the RCTs on the efficacy of MCP have been carried out in an English-speaking population, it is necessary to analyze the extent to which the Spanish participants accept the program and are comfortable with it, as well as their opinions and expectations about it, in order to improve adherence and future implementation.

The third objective of this proposed study will be to analyze whether the changes produced in the MIL dimensions (presence, search, comprehension, purpose, and mattering) predict the changes in anxiety, depression, quality of life, etc. In this study, we will use multidimensional measures of meaning to assess change in meaning in life. The MEMS (35) will allow us to evaluate the three dimensions of meaning (comprehension, purpose, and mattering), and the MLQ (36) will allow us to include two other dimensions (presence, search). Evaluating the effectiveness of MCP with multidimensional measures will allow us to find out whether it is effective for all the dimensions of meaning or, on the contrary, produces a change in one dimension (e.g., presence) but not in another (e.g., search). In addition, we will be able to verify which dimension of meaning best predicts the change in the patients' clinical measurements.

Another contribution of this proposed study is the application of MCP through videoconference. To the best of our knowledge, there are no studies on the efficacy of PCM *via* videoconference. This would allow us to take MCP to people who live in places where there are no psychotherapists, so that a greater number of people from very distant places could receive treatment. Some studies have described the advantages of online psychosocial interventions (55), such as compensating for geographical barriers and saving travel time (56). Currently, the number of psycho-oncological pilot studies of online interventions through videoconference in psycho-oncology is increasing. Results have highlighted participant engagement and effectiveness (57, 58). Moreover, a recent randomized control study (59) found similar effectiveness of both face-to-face and online psychotherapy for patients with a diagnosis of cancer with cancer distress. Finally, we must emphasize that we are going to carry out a follow-up at 6 months to confirm whether the results obtained after treatment are maintained, improve, or worsen in both treatment conditions.

However, our study could have some possible limitations. The first limitation we expect to find is the possible dropout rate in both treatment conditions. Treatment efficacy studies have found a dropout rate of 30% (9), which can interfere with the development of the study as well as the type of statistical analysis that we can perform. Another limitation is that the final sample may be composed mainly of older adult women, and because both treatment conditions will be carried out through video conference, this may make it difficult for them to adhere to the treatment conditions. Finally, the sample may be composed mainly of women with breast cancer, which will prevent the generalization of the results to men with other cancer diagnoses.

In sum, coping with cancer implies suffering, pain, hopelessness, low meaning in life, anxiety, and depression in many people (1–3). For this reason, it is necessary to develop effective psychotherapeutic treatments for people with cancer and survivors. Thus, it is necessary to verify the effectiveness of MCP by comparing it to well-established treatments. This will allow us to confirm whether MCP can become another well-established treatment for people with cancer.

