As we can see in the aforementioned RCTs, MCP has been compared to waiting list, TAU with the general practitioner, and active treatments such as supportive therapy. To expand the data supporting the efficacy of MCP for cancer patients, it would be necessary to compare MCP to other active therapies such as CBT. According to the data, no previous studies have compared MCP to active treatments such as CBT for cancer patients, which is the general objective of this study.

The aims of the proposed study are: the first objective is to verify the efficacy of the MCP intervention for Spanish participants with cancer in an RCT comparing it to CBT. The second objective is to analyze the feasibility and acceptance of MCP in Spanish participants with cancer. The third objective is to analyze whether the changes produced in the MIL dimensions (presence, search, comprehension, purpose, and mattering) will predict changes in anxiety, depression, quality of life, etc.

We propose the following hypothesis: (a) After the intervention, all the participants in the two treatment conditions (MCP vs. CBT) will improve on MIL, anxiety, depression, and quality of life; however, the participants in the MCP condition will improve more than those in the CBT condition; (b) After the intervention, both interventions will have good acceptance by the participants, but the MCP condition will have greater acceptance than the CBT condition; (c) The changes produced in the MIL dimensions (presence, search, comprehension, purpose, and mattering) after the intervention will be related to changes in anxiety, depression, and quality of life.

In this article, we present the study protocol.

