### Sample Size

The sample size for this study was generated from effect sizes found in other studies on MCP in participants with cancer, mainly meta-analyses. Dietrich (29) found medium effect sizes for meaning in life (*d* = 0.81), Quality of life (*d* = 0.60), anxiety (*d* = −0.47), and depressive symptoms (*d* = −0.50). These effect sizes are consistent with other studies on MCP in psychological treatments for other mental disorders, such as a meta-analysis by Vos et al. (12) on existential psychotherapies. Based on the results of these studies, we expect an effect size of 0.60 because the study design consists of two experimental groups. To calculate the sample size, we used the G^*^Power 3.1 software (30), taking into account an alpha of 0.05 and a statistical power of 0.80 on a two-tailed *t*-test. We need a sample size of 90 participants (45 participants per condition) to reach an effect size of 0.60 for meaning in life. Finally, we have considered possible sample loss during the treatment program, and based on studies of interventions with MCP, we expect a 30% dropout rate (9). Therefore, taking this outcome into account, our study requires a total sample size of 118 participants (59 participants per experimental condition).

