### Data Analyses

For data analysis, the Consort guidelines will be followed. Prior to analyzing whether MCP was more effective than CBT, we will verify that the two experimental conditions are similar in all the sociodemographic variables, such as age, sex, marital status, and education. In addition, we will verify that the two conditions are similar in terms of the percentage of participants who have received chemotherapy, radiotherapy, and surgery. To do so, we will use comparison of means (Student's t) for the continuous variables and chi square for the categorical variables. Moreover, the intention-to-treat principle will be used when analyzing pre- and post-treatment data and at the 6-month follow-up, using mixed-effects models with full information and maximum likelihood estimation. This method has been recommended due to its flexibility in handling missing data (51). To complement the MANOVA results and *post hoc* comparisons, effect sizes will be calculated using the standardized mean difference proposed by Cohen (52). These effect sizes will be calculated to assess changes within and between groups, all based on a pooled standard deviation. MANCOVAS will be carried out to find out if there are differences in the participants' response to the two experimental conditions depending on the type of medical treatment administered (surgery, chemotherapy, or radiotherapy), the stage of the cancer before the start of medical treatment, and whether the patient has a relapse during the psychological treatment. Moderation and mediation analyses will be performed to investigate possible mediators of change during treatment, such as meaning in life or coping style. Although per-protocol analyses (only analyses of data from participants who complete the treatment) suffer from selection bias, they will also be conducted because they allow conclusions to be drawn about the maximum efficacy of the intervention in participants who are fully compliant with treatment. However, when the trial is completed, the analytical methodology for controlled clinical trials will be reviewed before analyzing the data to select the most appropriate analytical procedures.

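### The Discussion counts 'equally effective' as support for MCP, but the trial is designed only for superiority and a non-significant difference from CBT could not show equality

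*Protocol article*

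**What the plan says.** Three parts of the protocol article set up a superiority trial:

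- Introduction, hypothesis (a): both arms are expected to improve, but "the participants in the MCP condition will improve more than those in the CBT condition".
- Sample Size: the calculation was done "taking into account an alpha of 0.05 and a statistical power of 0.80 on a two-tailed" t-test. For the effect, "we expect an effect size of 0.60 because the study design consists of two experimental groups". It gives 45 evaluable participants per arm for meaning in life, and 59 per arm enrolled after allowing for 30% dropout.
- Data Analyses: the question is framed by "Prior to analyzing whether MCP was more effective than CBT".

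The first paragraph of the Discussion then describes a wider set of favourable results. Its condition reads "if MCP is equally effective or more effective in reducing anxiety and depression and improving quality of life, hopelessness, and meaning in life". The inference it draws, whichever half of that condition is met, is worded cautiously: "this result would suggest that MCP could be a treatment of choice for people with cancer". No equivalence or non-inferiority hypothesis or margin appears in the article, and the limitations paragraph does not mention the point.

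**The concern.** A two-sided superiority test can show that MCP is better or worse than CBT. Without a margin it cannot show that the two are equal. Since the article plans no other between-arm inference, the obvious route to 'equally effective' would be a difference that failed to reach significance.

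Four of the five domains in the Discussion sentence (anxiety, depression, quality of life and hopelessness) are secondary outcomes, and the trial is sized on meaning in life alone. The comparator is a therapy that the same paragraph credits with effects on anxiety, depression and quality of life. The Introduction adds that "no previous studies have compared MCP to active treatments such as CBT for cancer patients", so no earlier head-to-head evidence is available to lean on. At stake is whether an inconclusive comparison with an established therapy, or one in which MCP is moderately worse, could be presented as support for MCP.

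**Working it through.** **Inputs from Sample Size:** two-sided alpha 0.05, power 0.80, d = 0.60, 45 evaluable and 59 enrolled per arm, 30% dropout; cited effects of 0.47 (anxiety) and 0.50 (depression). **Assumed, because the article gives none:** non-inferiority margins of 0.3, 0.5 and 0.6 SD, and a baseline-to-outcome correlation r of 0.5 to 0.7. Everything is in SD units.

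**1. The plan's own figure.** A two-sample, two-sided t-test with n = 45 per arm has noncentrality 0.60 × √(45/2) = 2.85 and power 0.804. It is the smallest n per arm that reaches 0.80, so the planned 45 is reproduced as a superiority sample size. A one-sided test would need 36.

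**2. Precision.** Half-width of the unadjusted 95% interval = t(0.975; 2n − 2) × √(2/n).

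- 45 per arm: 1.987 × 0.2108 = 0.419.
- 59 per arm (no loss at all): 1.981 × 0.1841 = 0.365.
- 41 per arm (59 × 0.7 = 41.3, if dropouts contribute nothing): 0.440.

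With baseline adjustment at 45 per arm, the half-width is 1.96 × √[(2/45)(1 − r²)], which is 0.358 for r = 0.5 and 0.295 for r = 0.7. Clustering by therapy group, not included here, would widen all of these.

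**3. What an observed zero leaves open.** At 45 per arm the interval runs from −0.42 to +0.42. Against the cited effects, 0.419/0.50 = 84% (depression) and 0.419/0.47 = 89% (anxiety). In the adjusted range, the smallest ratio is 0.295/0.50 = 59% and the largest 0.358/0.47 = 76%.

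**4. Non-significance when MCP is truly worse, one outcome, 45 per arm.** For a true deficit of 0.3 SD the noncentrality is 0.3 × √(45/2) = 1.42 and power is 0.291, so the test is non-significant in 71% of trials (63% at 59 per arm, 73% at 41). For 0.4 SD the figure at 45 per arm is 53%, and for 0.5 SD it is 35%.

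**5. Power to show non-inferiority if the therapies are truly equal.** Power = Φ(margin/√(2/n) − 1.96). At 45 per arm:

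- margin 0.3: Φ(1.42 − 1.96) = 0.30
- margin 0.5: Φ(2.37 − 1.96) = 0.66
- margin 0.6: Φ(2.85 − 1.96) = 0.81

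For 80% power at a 0.3 SD margin, n = 2 × [(1.96 + 0.842)/0.3]² = 175 per arm; at 0.5 SD, 63 per arm.

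**The case against.** The strongest reply is that the sentence is a hedged remark in the Discussion and not a decision rule. It says the result would suggest that MCP could be a treatment of choice, and nothing in Sample Size or Data Analyses makes equality a success criterion. That is right. A reader might infer that the plan formally accepts equality as success, or has already decided to report a null as equality. The article says neither. Data Analyses plans between-group effect sizes and a review of procedures before analysis, and an analysis plan not shown could add a margin. It could not, however, make 45 per arm adequate for a tight one.

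Second, the 71% applies to one outcome, whereas the sentence joins five. If MCP were 0.3 SD worse on all five and the outcomes were independent, all five would be non-significant in 0.709⁵ = 18% of trials. Positive correlation puts the figure between 18% and 71%. This stands, and the 71% should not be read as the chance that the whole condition is wrongly met.

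Third, the planned mixed model uses partial data and may adjust for baseline, so 0.42 SD may be pessimistic. This also stands. It narrows the interval to about 0.30 to 0.36 SD under the assumed correlations, before any widening from group clustering.

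Fourth, imprecision depends on the margin. At 0.5 or 0.6 SD the trial has 66% or 81% power. But such margins equal or exceed the whole effects cited for anxiety and depression and would be hard to defend.

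**Conclusion.** The wording is wrong as it stands and should be corrected. Only superiority is hypothesised, sized and analysed, no margin is stated, and a non-significant difference cannot support 'equally effective'. The unadjusted half-width of about 0.42 SD at 45 per arm covers most of the effects cited for anxiety and depression. Even the most favourable adjusted case considered leaves a deficit of about 0.30 SD open. These figures rest on a simple two-arm comparison with equal variances; the margins and correlations are assumptions.

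Two stronger inferences are not supported. One is that a null result is likely: the absence of earlier MCP versus CBT trials makes the effect unknown, not null. The other is that the article relies on within-arm improvement to establish equality: it does not, and regression to the mean after selection on the Purpose in Life test, which is not an outcome, cannot be quantified from the document.

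The problem limits what may be concluded. It does not affect randomisation, the endpoints, or the superiority analysis itself.

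**What to change.** Delete 'equally effective or' from the Discussion sentence. State there, and in the analysis plan, that a non-significant superiority test is inconclusive and will not be read as equality, and that the between-arm estimate will be reported with its 95% interval.

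If a similarity claim is wanted, fix a justified non-inferiority margin for each named outcome before unblinding. Claim similarity only where the 95% interval from the planned model excludes that margin, and acknowledge that the sample size is not powered for tight margins.

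The first option costs only wording. The second also requires a justification for each margin. Under either, the favourable conclusion open to the trial becomes narrower.

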## Ethics Statement

The study involves clinical experimentation with human participants. Researchers adhere to the Helsinki Convention and the Madrid Declaration of the World Psychiatric Association on clinical research. This project has been approved by the Ethics and Research Committee of the Valencian Institute of Oncology Foundation (CEIM: 2019-17). All participants/participants will be volunteers and give their informed consent to participate in the study.

## Abbreviations

MCP: Meaning-Centered Psychotherapy
RCT: Randomized Controlled Trial
TAU: Treatment as Usual
MCGP: Meaning-Centered Grief Psychotherapy
CBT: Cognitive Behavioral Therapy
CONSORT, Consolidated Standards of Reporting Trials SPIRIT, Standard Protocol Items: Recommendations for Interventional Trials
MLQ: Meaning in Life Questionnaire
MEMS: Multidimensional Existential Meaning Scale
OASIS: Overall Anxiety Severity and Impairment Scale
ODSIS: Overall Depression Severity and Impairment Scale
HS: Hopelessness Scale
PANAS: The Positive and Negative Affect Schedule
QLI: Quality of life index-Spanish version
OTSM: Opinion and Expectations of Treatment Scale
MINI-MAC: Mini-Mental Adjustment to Cancer Scale
PTGI: Posttraumatic Growth Inventory
MANOVA: Multivariate analysis of variance
ANOVA: Analysis of variance.
